#### Impairment assessment

The impairment assessment, completed after each drive on each test day (see Fig. 1), comprises assessments of cognitive performance, a pupillometry assessment, and measures of subjective state as outlined below.

##### Cambridge Neuropsychological Test Automated Battery (CANTAB)

Participants will complete three cognitive tests drawn from the CANTAB (Cambridge Neuropsychological Test Automated Battery, Cambridge Cognition, Ltd., UK) system designed specifically for neuropsychological testing and academic research. Tests include (1) Rapid visual information processing (RVP), an assessment of sustained attention; (2) reaction time (RTI), an assessment of motor and mental response speed and accuracy; and (3) spatial working memory (SWM), a visuospatial working memory task with notable executive function demands. Cognitive data will be analysed as change from t1 to t2 and from t1 to t3. All CANTAB assessments will be administered on an iPad in a quiet area of the testing site. Each task and its associated outcome measures are described below in Table 2:

**Table 2 Tab2:** Description of CANTAB tests being used to assess cognitive function

Task	Measure	Outcomes
Rapid Visual Information Processing (RVP)	A sensitive measure of sustained attention (focus) which is integral to safe driving behaviour	A prime: A measure of signal detection sensitivity to the target sequence. Higher scores indicate better performance Response latency: The median response time (ms) for correctly identified target sequences Probability of false alarm: The proportion of incorrect responses, calculated as the number of false alarms divided by the total number of false alarms plus correct rejections
Reaction time (RTI)	Measures motor and mental response speed, including reaction time, and response accuracy. Relates to driver ability to respond quickly and appropriately to visual stimuli	Reaction time: Median time (ms) taken to release the response button after stimulus presentation. Calculated across correct trial Total errors: Total number of trials in which a response error occurred
Spatial working memory (SWM)	Measures visuospatial working memory, placing demands on executive function and assessing strategy use and errors. Reflects visual search efficiency in drivers as well as executive function which incorporates key cognitive skills	Between errors: Number of times a participant revisits a box where a token was previously found. Calculated across four, six, and eight token trials Strategy (6–8 boxes): Number of times a participant starts a new search from the same box they started with previously. Lower scores indicate greater strategy use

##### Pupillometry

Spontaneous and involuntary pupil movement will be evaluated using the F3D Fit-for-Duty test (AMTech Pupilknowlogy, Dossenheim, Germany). The F3D uses head-mounted binocular video goggles to assess fatigue and drug effects. The two pupillometry outcomes to be assessed include the pupillary light reflex (PLR), a measure of the pupillary response to light being used to assess potential drug impairment, and pupillary unrest index (PUI), a measure of pupillary oscillation being used to assess fatigue. The PUI and PLR values are generated automatically by a proprietary algorithm and will be analysed as a proportion of participants showing either impairment or fatigue per timepoint.

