#### Driving performance metrics

The primary outcome measure for both phases of the trial is the standard deviation of lateral position (SDLP), a measure of lane weaving, swerving, and overcorrecting that is highly sensitive to alcohol and drug effects and is widely considered to be the gold-standard measure of driving performance in human psychopharmacology research [22–24]. SDLP and all secondary driving performance metrics are described below in Table 1. The analysis metric is change from pre-dosing to post-dosing (i.e. t2–t1 and t3–t1) for all measures.

**Table 1 Tab1:** Description of driving performance outcome measures

Domain	Measure	Outcome(s)
Driving performance (objective)	Standard deviation of lateral position (primary outcome)	Standard deviation of vehicle lateral position in centimetre (mean)
	Number of lane excursions	Number of times (count) one or more vehicle wheels exceeds the lane boundary
	Speed adherence	Mean speed (km/h) during driving, standard deviation of speed (km/h), and % time above the speed limit
	Steering variability	Steering reversal rate (number of directional changes per minute) and steering entropy (standard deviation of steering angle)
	Harsh acceleration	Count of rapid longitudinal acceleration events where acceleration is ≤ 0.35 g and < 0.58 g (harsh) or ≥ 0.58 g (very harsh)
	Harsh braking	Count of harsh braking events where deceleration is ≤ −0.75 g (extremely harsh), < −0.75g and ≤ −0.5g (very harsh) or ≤ −0.45g (harsh)
Ocular behaviour	Gaze behaviour (entropy)	Stationary gaze entropy and gaze transition entropy
	Rate and duration of visual fixations	Number of fixations (count per minute) and time of fixations (ms) where driver holds their gaze at a specific point on the roadway
	Microsleeps	Frequency (count) of long eye closures lasting ≥ 500 ms (NB: also adverse event indicator)
Driving performance (adverse event)	Instructor termination of drive	Number of times (count) a drive was terminated by the driving instructor
	Instructor intervention during drive	Number of times (count) the driving instructor had to intervene during a drive
Driving performance (subjective)	Instructor rating of fitness to drive	Instructor rating of fitness to drive (yes/no) at the end of each drive (proportion)

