### Statistical analysis {20a, 20b, 20c}

Participant demographic and baseline characteristics will be summarised separately by study phase and treatment condition, where applicable. Continuous variables will be summarised using means and standard deviations (SD), and where appropriate, medians and interquartile ranges (IQR) will also be reported. Categorical variables will be summarised using frequencies and percentages (%). No formal hypothesis testing of demographic variables will be conducted; summaries are intended to describe the study population and assess baseline comparability across groups. Analysis of primary and secondary outcome measures will be conducted using a series of linear mixed-effects models (continuous data), Poisson or negative binomial generalised linear mixed models (count data), logistic mixed-effects models (binary data), or time-binned mixed models and linear regression (ocular data). Post hoc tests with Bonferroni adjustments will be conducted where significant main effects or interaction effects are observed. No deletion or imputation will be used where data is missing at random, as mixed models inherently accommodate incomplete repeated measures. Sensitivity analysis will be conducted using delta-adjustment for nonrandom missing data. Exploratory subgroup analyses will test for differences in change in outcome measures over time as a function of health condition, route of administration, and gender (phase 1 only). All statistical analyses will be conducted using SPSS (IBM Corp, Armonk, NY, USA) and R, and tests will be set two-tailed with a conventional level of significance of *p* < 0.05.

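### Pupillometry is analysed as the proportion flagged impaired or fatigued, which loses the size of within-person change that the device's values could show

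*Protocol article*

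**What the plan says.** The protocol article, under Impairment assessment – Pupillometry, names two outcomes. The PLR is "a measure of the pupillary response to light being used to assess potential drug impairment" and the PUI is "a measure of pupillary oscillation being used to assess fatigue". On the output it says: "The PUI and PLR values are generated automatically by a proprietary algorithm". On the analysis it says that they "will be analysed as a proportion of participants showing either impairment or fatigue per timepoint". The section gives no measurement scale, cut-off or expected flag rate.

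The other parts of the same assessment battery are handled differently. For the CANTAB tests: "Cognitive data will be analysed as change from t1 to t2 and from t1 to t3". The section on subjective assessments uses the same two changes for its mean scores. The Statistical analysis section provides linear mixed-effects models for continuous outcomes and logistic mixed-effects models for binary ones.

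**The concern.** By the article's own description, both outcomes are graded quantities: a response to light and an index of oscillation. The plan analyses them as a yes/no classification. Three things follow.

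- A shift that stays on one side of the cut-off is not counted, whatever its size.
- A participant already flagged at drive 1 cannot show worsening. This is a realistic possibility in patients on stable daily treatment.
- The cut-off is unstated and the algorithm is proprietary, so a null result could not be told apart from an insensitive threshold.

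The Discussion says the supporting assessments are meant to help define levels of impairment and to find useful indicators of it. A flag has no levels. With 72 patients in phase 1 and 24 volunteers in phase 2, there is little information to spare. This is not a gap left to a later document: the article states the form of the analysis.

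**Working it through.** **Inputs from the article.** N = 72 (phase 1) and 24 (phase 2), with a two-sided 5% level. The correlation among repeated measures is 0.6 (phase 1) and 0.5 (phase 2). Both correlations are given in Sample size for the standard deviation of lateral position (SDLP), not for pupillometry, and are borrowed here.

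**Assumed.** The measure is normal and is cut once. The proportion flagged, p, ranges from 5% to 50%. None of this is in the documents.

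**The plan's own figure.** There is none for pupillometry. The SDLP calculation from which the correlations come does reproduce. With λ = f²·N·m·ε/(1−ρ), phase 1 gives 0.15² × 72 × 6 × 0.6/0.4 = 14.58 on (3, 213) degrees of freedom and power 0.903; the smallest N for 90% is 72. Phase 2 gives 0.25² × 24 × 12 × 0.6/0.5 = 21.6 and power 0.941, so its stated 90% is met.

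**Step 1: single-timepoint comparison.** Let c be the normal quantile at 1−p and φ the normal density. The efficiency of the flag relative to the continuous value is

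E₁ = φ(c)² / [p(1−p)].

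- p = 0.5: 0.3989²/0.25 = 0.637, a loss of 36%.
- p = 0.05: 0.1031²/0.0475 = 0.224, a loss of 78%.

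**Step 2: within-person change.** Both analyses gain from pairing, but the flags correlate less strongly than the values. If r_b is the correlation of the two flags under a bivariate normal with correlation ρ, then

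E₂ = E₁ × (1−ρ)/(1−r_b).

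- p = 0.5, ρ = 0.5: r_b = 0.333, so 0.637 × 0.5/0.667 = 0.48, a loss of 52%.
- p = 0.05, ρ = 0.6: r_b = 0.274, so 0.224 × 0.4/0.726 = 0.12, a loss of 88%.

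| Flagged (assumed) | Loss, single timepoint | Loss, change, ρ = 0.5 | Loss, change, ρ = 0.6 |
|---|---|---|---|
| 50% | 36% | 52% | 57% |
| 25% | 46% | 61% | 65% |
| 20% | 51% | 65% | 69% |
| 10% | 66% | 77% | 80% |
| 5% | 78% | 86% | 88% |

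**Step 3: the same loss as power.** Take the shift d (in SD units) that gives 90% power on the continuous paired change: d = (1.960 + 1.282) × √[2(1−ρ)/N].

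- Phase 1: 3.242 × √(0.8/72) = 0.34.
- Phase 2: 3.242 × √(1/24) = 0.66.

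Then analyse the same shift as a paired proportion (McNemar-type test, normal approximation). Here D is the proportion of discordant pairs and δ the difference in proportions: power = Φ{[|δ|√N − 1.960√D]/√(D − δ²)}.

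| Flagged at t1 (assumed) | Power, N = 72, ρ = 0.6 | Power, N = 24, ρ = 0.5 |
|---|---|---|
| 50% | 53% | 51% |
| 25% | 49% | 51% |
| 10% | 34% | 38% |
| 5% | 24% | 27% |

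An effect with 90% power on the continuous scale therefore has, at best, about even odds of detection as a flagged proportion.

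**The case against.** The strongest defence is that a fit-for-duty classification is a sensible thing to report in a trial about impairment and road safety, and that pupillometry is one non-primary part of a large battery. Both points stand. They are reasons to keep the flag and to rate the matter as minor. They do not justify making the flag the only named analysis.

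It can also be said that the article does not exclude a continuous analysis, and that the planned logistic mixed model would use each person's flags across drives. That is so, and within-person information is not lost altogether. What such a model cannot recover is the size of a change, or any change short of the cut-off.

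A further objection is that the device's scale is unknown and its values may not be exportable. This stands as a condition on the remedy.

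A reader might infer a contradiction with the sentence "The analysis metric is change from pre-dosing to post-dosing (i.e. t2–t1 and t3–t1) for all measures". The documents do not support that. The sentence sits under Driving performance metrics, directly after the reference to the table of driving outcomes. The cognitive, subjective and concentration sections each set their own metric, and for concentrations it is a summary per timepoint. In context, the sentence covers the driving measures.

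A reader might also take a fixed loss as a property of this trial. It is not: the flag rate, the distribution and the pupillometry correlation are all unstated.

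**Conclusion.** The point holds as a minor improvement to a secondary analysis. The article commits to an inefficient form of analysis for two graded measures, gives no reason, and departs from how it treats the adjacent cognitive and subjective measures.

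The direction of the loss is not in doubt if the underlying values are graded. Its size is conditional: about 36–78% at a single timepoint and about 52–88% for within-person change. Both ranges assume normality, a single cut and 5–50% flagged, and the second also uses the SDLP correlations. The second range is closer to the comparison the trial makes. A proprietary rule that is not a single cut would give other figures. Nothing here touches the primary outcome or the sample size, and no internal contradiction is claimed.

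**What to change.** Name continuous PLR and PUI as the analysed pupillometry outcomes, as change from t1 to t2 and from t1 to t3, using the linear mixed model already in the Statistical analysis section. Log-transform the PUI if it is skewed. Report the flagged proportions as supportive, separately for impairment (PLR) and fatigue (PUI).

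The cost is a data export and two extra model fits. It depends on the device's continuous values being saved and exportable. The Trial status section expects recruitment to finish in mid-2026, so the sponsor should confirm this now. If only the flags can be exported, the article or analysis plan should say so and give that as the reason for analysing proportions.

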##### Subjective assessments and questionnaires

Participants will complete a suite of subjective state measures during each impairment assessment. These include the Karolinska Sleepiness Scale (KSS) [25], Perceived Driving Quality/Effort Scale (PDQ/PDE), Drug Effects Questionnaire (DEQ), and NASA Task Load Index (TLX) [26]. In phase 2, participants will also complete the Brief Biphasic Alcohol Effects Scale (B-BAES) [27]. Mean scores on the KSS, PDQ/PDE, DEQ, TLX, and B-BAES will be analysed as change from t1 to t2 and from t1 to t3. The TLX is not intended as a stand-alone measurement but rather an indicator of workload during the driving task, so results will be interpreted in relation to driving performance metrics as described above.

#### Oral fluid and blood

On each test day in phase 1, patients will provide three oral fluid samples and three blood samples. Oral fluid samples will be collected using the Securetec DrugWipe Twin. Blood samples will be frozen at −80 °C for long-term storage at Swinburne University and analysed later via liquid chromatography—mass spectrometry (LC–MS) for THC, 11-hydroxy-THC (11-OH-THC), 11-nor-9-carboxy-THC (11-COOH-THC), and cannabidiol (CBD) by the Victorian Institute for Forensic Medicine (VIFM) according to previously published methods [28]. In phase 2, participants will provide breathalyser samples throughout the day (as shown in Fig. 1) to obtain BAC readings. Cannabinoids’ concentrations and BAC readings will be analysed as mean (SD) or median (IQR) values at each timepoint.

### Data collection {18b} and management {19}

Our staff are highly trained in the collection, management, storage, and confidentiality of data to ensure compliance with all policies and regulations. Identifiable patient data will be stored electronically in password-protected files only accessible to study investigators. Coded paper records will be kept in designated, locked storage areas. Study case report forms are primarily electronic and hosted on Qualtrics and will be regularly reviewed for completeness and compliance. Driving data will be checked for completeness of recordings and backed up after each session. All other data will be backed up at regular intervals to minimise the risk of data loss.

### Statistical analysis {20a, 20b, 20c}

Participant demographic and baseline characteristics will be summarised separately by study phase and treatment condition, where applicable. Continuous variables will be summarised using means and standard deviations (SD), and where appropriate, medians and interquartile ranges (IQR) will also be reported. Categorical variables will be summarised using frequencies and percentages (%). No formal hypothesis testing of demographic variables will be conducted; summaries are intended to describe the study population and assess baseline comparability across groups. Analysis of primary and secondary outcome measures will be conducted using a series of linear mixed-effects models (continuous data), Poisson or negative binomial generalised linear mixed models (count data), logistic mixed-effects models (binary data), or time-binned mixed models and linear regression (ocular data). Post hoc tests with Bonferroni adjustments will be conducted where significant main effects or interaction effects are observed. No deletion or imputation will be used where data is missing at random, as mixed models inherently accommodate incomplete repeated measures. Sensitivity analysis will be conducted using delta-adjustment for nonrandom missing data. Exploratory subgroup analyses will test for differences in change in outcome measures over time as a function of health condition, route of administration, and gender (phase 1 only). All statistical analyses will be conducted using SPSS (IBM Corp, Armonk, NY, USA) and R, and tests will be set two-tailed with a conventional level of significance of *p* < 0.05.

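### The rule to subtract drive 1 from drives 2 and 3 for every measure cannot be combined with the count and logistic mixed models, and it conflicts with the no-deletion statement when drive 1 is missing

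*Protocol article*

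**What the plan says.** All references are to the Protocol article.

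- **Metric.** Driving performance metrics, just before Table 1: "The analysis metric is change from pre-dosing to post-dosing (i.e. t2–t1 and t3–t1) for all measures".
- **Models.** Statistical analysis {20a, 20b, 20c}: linear mixed models for continuous data, then "Poisson or negative binomial generalised linear mixed models (count data), logistic mixed-effects models (binary data), or time-binned mixed models and linear regression (ocular data".
- **Missing data.** Same section: "No deletion or imputation will be used where data is missing at random, as mixed models inherently accommodate incomplete repeated measures". A delta-adjusted sensitivity analysis is planned for data not missing at random.
- **Outcome definitions.** Table 1 mixes scales. Lane excursions are a bare count ("Number of times (count) one or more vehicle wheels exceeds the lane boundary"), as are harsh acceleration, harsh braking, microsleeps and instructor interventions. Termination is a further count ("Number of times (count) a drive was terminated by the driving instructor"). Fitness to drive is binary ("Instructor rating of fitness to drive (yes/no) at the end of each drive (proportion"). Steering variability, by contrast, includes a measure per unit of time ("Steering reversal rate (number of directional changes per minute"), and so does the number of fixations.
- **Exposure.** Participant timeline {13} plans three 20-minute drives per test day, and Table 1 foresees that the instructor may end a drive.

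**The concern.** The metric sentence and the model sentence each fix part of the same analysis, and for counts and yes/no outcomes they exclude each other. A later analyst would have to break one of them. That could mean modelling raw values with the generalised models, or keeping the differences and moving to a linear model. These give different estimands: a rate ratio or odds ratio in the first case, a mean difference in the second. The choice would then be made after the data are in, for most of the secondary driving outcomes.

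The same metric sentence also bears on missing data. A mixed model accommodates incomplete repeats when the repeats are the response. If drive 1 has already been subtracted, losing drive 1 means losing that day's two differences, and post-dose data that were observed are discarded. This part reaches the primary outcome.

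**Working it through.** **1. How many outcomes are affected.** Table 1 has 12 rows: SDLP (primary) and 11 secondary rows. Counts: lane excursions, harsh acceleration, harsh braking, microsleeps, termination, intervention (6). Binary: fitness to drive (1). Total 6 + 1 = 7 of 11. Microsleeps sit in the ocular domain; if they go to the ocular models instead, the number is 6 of 11, still a majority.

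**2. Differences against the model's support.** Poisson and negative binomial models need values 0, 1, 2, … Let pre- and post-dose counts be independent Poisson with the same mean μ (no drug effect; the values of μ are assumed, as the article gives none). Then P(difference < 0) = [1 − e^(−2μ) I₀(2μ)] / 2, where I₀ is the modified Bessel function.

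| Mean per drive, pre → post | P(difference < 0) |
|---|---|
| 0.5 → 0.5 | 0.27 |
| 1 → 1 | 0.35 |
| 2 → 2 | 0.40 |
| 4 → 4 | 0.43 |
| 2 → 3 | 0.25 |
| 4 → 6 | 0.21 |

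The last two rows (unequal means, from the general distribution of a Poisson difference) show that negatives stay common when the true mean rises by half. A single negative value is enough: a Poisson fit to the differences −1, 0, 2, 1, −2, 3 has log-likelihood minus infinity. For a yes/no rating the difference is −1, 0 or 1, and a logistic model needs two values.

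**3. Missing drives.** On one test day:

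| Missing | Drive-level response keeps | Change scores keep |
|---|---|---|
| Drive 1 | drives 2 and 3 | nothing |
| Drive 2 | drives 1 and 3 | t3–t1 |
| Drive 3 | drives 1 and 2 | t2–t1 |

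Only the first row conflicts with the no-deletion statement. If each drive is missing independently with probability q (assumed), the usable share of post-dose values is 1 − q at drive level and (1 − q)² as change scores. Phase 1 has 72 × 2 days × 2 post-dose drives = 288 planned post-dose values.

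| q | Drive level | Change scores | Observed values discarded |
|---|---|---|---|
| 5% | 95% (273.6) | 90.25% (259.9) | 13.7 |
| 10% | 90% (259.2) | 81% (233.3) | 25.9 |

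These are records, not information: a post-dose value without its own drive 1 contributes less to the contrast than a complete pair.

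**4. The plan's own sample size.** Sample size {14} counts six repeated measurements in phase 1, so drive 1 is a response there. With f = 0.15, n = 72, m = 6, correlation 0.6, non-sphericity 0.6 and alpha 0.05: noncentrality = 0.15² × 72 × 6 × 0.6 / (1 − 0.6) = 14.58; df1 = 5 × 0.6 = 3; df2 = 71 × 5 × 0.6 = 213; power = 0.903. The stated 90% reproduces, and it does so on drive-level values. The point here does not dispute it.

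**5. Shortened drives.** If a drive stopped after k of 20 minutes were analysed as a full one, its apparent rate ratio is the true ratio × k/20. For a true ratio of 2 and k = 5, 10, 15 this gives 0.5, 1.0, 1.5. Averaged over post-dose drives with a true ratio of 1.5, a share p stopped halfway and the same event rate in all drives, the apparent ratio is 1.5 × (1 − 0.5p): 1.485 at p = 2%, 1.35 at p = 20%. All of these rates are assumptions; the article gives no termination frequency.

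**The case against.** The best defence is that change already means a model contrast. The abstract says the mixed and generalised linear mixed models will assess change over time, the missing-data sentence speaks of repeated measures, and the sample size calculation treats all three drives per day as measurements. On that reading the analysis is sound and the missing-data statement is correct under missing at random. This may well be the intent. It does not settle the matter, because the metric sentence writes out a subtraction and extends it to all measures. Another document cannot agree with both sections as they stand.

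It also stands that SDLP is continuous. A linear mixed model can be fitted to its change scores, so the model conflict does not touch the primary outcome; only the missing-drive-1 point does.

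Stronger readings that the document does not support:

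- *That counts will be analysed without an exposure offset and so understate impairment.* The article is silent on offsets, a detail commonly left to the full protocol or analysis plan. The direction follows only if a shortened drive is treated as a full one, and the size cannot be known from the text. Terminations, interventions and fitness ratings are outcomes in their own right, so the worst drives are not lost from view.
- *That the ocular regression ignores clustering.* Linear regression is named next to mixed models, with nothing said about where it applies; the correlation of 0.6 is given for SDLP, not for ocular outcomes.
- *That termination is wrongly a count.* Over several drives a number of terminations is a legitimate count; this is labelling.

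**Conclusion.** The point holds as a contradiction between two stated rules. The subtraction metric cannot be used with the Poisson, negative binomial or logistic mixed models, which affects seven of the 11 secondary rows of Table 1 (six if microsleeps are handled as ocular data). That conclusion needs no assumption beyond reading the metric sentence as written. The conflict with the no-deletion statement is real but narrower: it arises only when drive 1 is missing, and then it costs both post-dose values of that day for every outcome in Table 1, SDLP included. Its size depends on the missing-drive rate, which is not given.

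This should be corrected before analysis. It does not invalidate the primary analysis or the sample size. The offset is a recommended addition, not an error shown in the text.

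**What to change.** Amend the metric sentence in Driving performance metrics so that the values at drives 1, 2 and 3 are the response in every model, and change is the model contrast of drive 2 versus 1 and drive 3 versus 1: a mean difference for continuous outcomes, a rate ratio for counts, an odds ratio for yes/no outcomes. The missing-data sentence then holds as written under missing at random. The CANTAB section uses similar change wording and includes error counts, so the same clarification is useful there.

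As an addition, model lane excursions, harsh events, microsleeps and interventions with log(minutes driven) as an offset, and say how a terminated drive enters these models. An offset puts the counts on a common per-minute scale. It does not fully resolve stopping that is triggered by the very events being counted, so terminations should be reported beside these results.

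The cost is wording and code, with no new participants or procedures. Drive duration has to be available for the outcomes that Table 1 already defines per minute; recording of distance is not stated, so minutes are the safer choice of exposure. Recruitment is expected to run to mid-2026 (Trial status), so the change can be made and dated before the data are analysed.

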### Sample size {14}

For phase 1, a sample size of *n* = 72 will allow us to detect a small magnitude change (*f* = 0.15) in our primary outcome measure—the standard deviation of lateral position—with 90% power assuming one group (i.e. all patients collapsed into a single group), six repeated measurements (three drives over 2 days), an estimated correlation among repeated measures of 0.6, and a non-sphericity correction of 0.6. The effect size used for this power calculation was derived from a previous on-road driving study with synthetic THC (dronabinol) [15] and conservatively reduced to account for the fact that treatment effects associated with prescribed medical cannabis may be considerably smaller than those seen previously in healthy volunteers given an intoxicating dose of THC. For phase 2*,* a sample size of *n* = 24 will allow us to detect a medium effect size (*f* = 0.25) with 90% power assuming one group, 12 repeated measurements (12 drives over 4 days of testing), an estimated correlation among repeated measures of 0.5, and a non-sphericity correction of 0.6. This effect size (*f* = 0.25) is equivalent to the level of impairment considered meaningful in a recent meta-analysis of 80 publications comprising 1534 driving or cognitive performance outcomes [13]. All sample size calculations were done in G*Power 3.1.

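### Bonferroni for the post hoc tests is valid but needlessly conservative: Holm's step-down procedure gives the same error control and about 1 to 11 points more power for the drive 3 contrast

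*Protocol article*

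**What the plan says.** The Statistical analysis section of the protocol article names one multiplicity method: "Post hoc tests with Bonferroni adjustments will be conducted", wherever a main effect or an interaction is significant. It also says that "tests will be set two-tailed with a conventional level of significance of" 0.05. Bonferroni in its ordinary sense is the single-step procedure, and no step-down version is mentioned.

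Under Driving performance metrics the contrasts of interest are set: "The analysis metric is change from pre-dosing to post-dosing (i.e. t2–t1 and t3–t1) for all measures". The cognitive tests follow the same pattern: "Cognitive data will be analysed as change from t1 to t2 and from t1 to t3". Each of these measures therefore has at least two follow-up comparisons.

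The Sample size section gives power for Phase 1 only for the overall repeated-measures test. It says that 72 patients "will allow us to detect a small magnitude change" (f = 0.15) with 90% power, assuming one group and "six repeated measurements (three drives over 2 days), an estimated correlation among repeated measures of 0.6, and a non-sphericity correction of 0.6". No power is claimed for an individual contrast.

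**The concern.** With two contrasts, Bonferroni tests each at 0.05/2 = 0.025, even when the other has already been rejected. Holm tests the smaller p-value at 0.025 and, if that is rejected, the larger at 0.05. It needs no further assumption, so on rejections Bonferroni is dominated.

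The loss falls mainly on the weaker contrast. The Participant timeline section places drive 2 at the expected peak of effects, so t3–t1 is probably the weaker one. Drive 3 is also the later of only two post-dose drives and carries the evidence on whether an effect persists. In a road-safety study, a drive 3 effect that just misses a stricter threshold could be read as recovery.

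**Working it through.** **Step 1. Reproduce the article's own figure.** For a one-group repeated-measures test, with f = 0.15, N = 72, m = 6, correlation ρ = 0.6 and non-sphericity correction ε = 0.6 (all from Sample size):

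- λ = f²·N·m·ε/(1 − ρ) = 0.0225 × 72 × 6 × 0.6/0.4 = 14.58
- df1 = (m − 1)ε = 3; df2 = (N − 1)(m − 1)ε = 213
- Power at α = 0.05 is 0.903. With N = 71 it is 0.899, so 72 is the smallest N that reaches 90%.

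The stated figure reproduces. It concerns the omnibus test and does not depend on the post hoc method.

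**Step 2. Inputs for the contrasts.** N = 72, ρ = 0.6 and two-sided 0.05 come from the article. My assumptions are:

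- compound symmetry, with SD 1 per measurement;
- each drive averaged over the two tracks;
- f = 0.15 applied to the three drive means (0, d, r·d), where r is the drive 3 effect as a share of the drive 2 effect;
- paired t tests standing in for the mixed-model contrasts.

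The variance of a two-track drive mean, apart from the person effect, is (1 − 0.6)/2 = 0.2. A change score then has variance 0.4 and SD 0.632. Its standard error is 0.632/√72 = 0.0745.

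The drive 2 effect is d = 0.15/SD(0, 1, r). This is 0.318 for r = 1, 0.363 for r = 0.63 and 0.367 for r = 0.5.

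**Step 3. Power for t3–t1.** Worked example, r = 0.5: the drive 3 effect is 0.184 and the noncentrality is 0.184/0.0745 = 2.46. On 71 degrees of freedom, power is 57.1% at level 0.025 and 68.1% at 0.05. Drive 2 has noncentrality 4.93 and is rejected at 0.025 in over 99% of trials, so Holm nearly always tests drive 3 at 0.05.

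Simulation (100,000 trials per row, post hoc tests only after a significant omnibus F):

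| r | Bonferroni | Holm | Gain (points) |
|---|---|---|---|
| 1.0 | 97.4% | 98.6% | 1.1 |
| 0.75 | 89.3% | 93.6% | 4.4 |
| 0.63 | 78.0% | 85.6% | 7.6 |
| 0.6 | 74.0% | 82.6% | 8.6 |
| 0.5 | 57.0% | 68.0% | 11.0 |
| 0.4 | 37.7% | 49.0% | 11.4 |

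On a single test day power is lower throughout, and the gain is 5.2 points at r = 1, 10.5 at r = 0.6 and 10.1 at r = 0.5.

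**Step 4. Ceiling.** For two contrasts the largest possible gain for the second is the greatest difference between power at 0.05 and at 0.025. On 71 degrees of freedom this is 11.5 points (44.8% to 56.3%).

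**Step 5. Error control.** With no effect at either drive, and the two contrasts tested without the omnibus gate, the family-wise error is the same for both methods: 4.7% in simulation. With an effect at drive 2 only (f = 0.15), false rejections at drive 3 rise from 2.5% to 4.8%, within the 5% limit.

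**The case against.** The strongest reply is that nothing here is wrong. Bonferroni is valid, prespecified and applied only to post hoc tests. The article promises no power for single contrasts, so no stated figure fails. All of that stands, and it limits the point to an efficiency improvement.

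A second reply is that the gain depends on the scenario chosen. This also stands. A reader might take 10 points as the typical loss, but that requires drive 2 to be rejected almost always and drive 3 to have middling power. A reader might also cite a drive 2 effect of 0.318 SD with 0.20 SD at drive 3, where power goes from 65% to 75%. Those effects correspond to f = 0.131, below the planned 0.15. Likewise, 0.20 SD at both drives gives a rise from about 49% to 61% in power to detect both contrasts, but f is then 0.094, and t3–t1 alone gains under 6 points.

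Third, the article's aim includes how large the effect is, so intervals matter. Bonferroni has simple simultaneous intervals that agree with its tests, and Holm does not. This is a real cost, and the fix has to deal with it.

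Fourth, the article does not say how many comparisons form a family, and an analysis plan may settle that. Two is my reading of the stated contrasts. The figures should not be carried over to larger families, or to track, condition or treatment comparisons, without a separate calculation.

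**Conclusion.** The point holds as a cheap improvement of low severity. For the two contrasts of one outcome, Holm gives the same family-wise control as Bonferroni and never rejects less. At the Phase 1 design effect, averaged over both tracks, power for t3–t1 rises by about 1 point with equal effects, 7 to 8 points when drive 3 has about 63% of the drive 2 effect, and about 11 points when it has half.

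These sizes rest on the unstated drive 3 to drive 2 ratio, on compound symmetry, and on a family of two. The documents do not support a reading that the analysis is invalid, that Phase 1 is underpowered because of Bonferroni, or that about 10 points are lost as a rule.

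**What to change.** In the Statistical analysis section, replace Bonferroni with Holm as the adjustment for post hoc tests. State that the t2–t1 and t3–t1 contrasts of one outcome form one family, and that significance is taken from the Holm-adjusted p-values.

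State also what the confidence intervals are, since either choice can disagree with the test:

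- **Unadjusted 95% intervals**, labelled descriptive. If the smaller p-value lies between 0.025 and 0.05, its interval excludes zero but Holm does not reject.
- **Bonferroni-simultaneous (97.5%) intervals.** If one contrast is rejected at 0.025 and the other has p between 0.025 and 0.05, Holm rejects the second but its interval includes zero.

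A sentence noting that intervals and Holm decisions may differ is enough.

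The cost is one changed word, a sentence defining the family and a sentence on intervals. Holm is built into R, which the article already names. No further participants or data are needed. Recruitment is expected to run to mid-2026, so the change should be dated and documented before the outcome data are analysed.
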